# The effect of prebiotic fibre on the gut microbiome and surgical outcomes in patients with prosthetic joint infection (PENGUIN) - study protocol for a randomised, double-blind, placebo-controlled trial (ACTRN12623001273673)

**DOI:** 10.1186/s12937-024-01034-z

**Published:** 2024-10-25

**Keywords:** Prosthetic joint infection, Gut dysbiosis, Resistant starch, Prebiotic fibre, Two-stage revision, Arthroplasty, Zonulin levels

## Abstract

**Background:**

Prosthetic Joint Infection (PJI) is the most devastating complication of arthroplasty surgery and affects 1–5% of patients. Despite strict adherence to aseptic protocols and preventive measures, infection is the most common reason for revision arthroplasty, and the incidence is increasing. Treatment of PJI is challenging and often requires repeated major surgeries with sequentially poor results. The continued occurrence of PJI, and persistence after treatment, brings into question the current treatment paradigm. Preclinical evidence suggests a link between altered gut health and the risk of PJI in arthroplasty patients. Resistant starches helps to restore gut physiology by enhancing the beneficial microbiome and producing short-chain fatty acids, which have several health-conferring properties. The primary aim of this study is to investigate the effect of a commercially available prebiotic fibre formulation on the gut microbiome in PJI patients planned for a two-stage revision surgery.

**Methods:**

A double-blind placebo-controlled trial will assess the effect of 8-week supplementation of a commercially available prebiotic supplement in patients presenting with first-time PJI undergoing two-stage revision surgery. The supplementation phase will start after the first stage revision, and 80 patients will be randomised to receive either a test product (34 g of resistant starch) or a placebo (custard powder) daily for eight weeks. Stool and blood specimens will be collected at baseline, four weeks and eight weeks after the first-stage surgery and once at second-stage surgery. Gut microbiome profile, inflammatory cytokines and gut permeability biomarkers will be measured. Tissue specimens will be collected intra-operatively during first and second-stage surgeries. Baseline dietary patterns and gut symptoms will be recorded using validated questionnaires. Treatment outcomes will be reported for both cohorts using the Delphi criterion at one and two years after second-stage surgery.

**Discussion:**

This will be the first study to investigate the relationship between gut health optimisation and preventing PJI recurrence in arthroplasty patients. If supplementation with resistant starch improves gut health and reduces systemic inflammation, optimising the gut microbiome will be a recommended preoperative management strategy for arthroplasty patients.

**Trial registration no:**

ACTRN12623001273673.

**Supplementary Information:**

The online version contains supplementary material available at 10.1186/s12937-024-01034-z.

Arthroplasty or joint replacement is a life-changing surgery for millions of people with end-stage arthritis. Successful joint replacement provides pain relief and restores function and independence, significantly improving the patient’s quality of life. With the increasingly aged population, longer life expectancy and lifestyle factors, the demand for joint replacement is increasing exponentially. By 2030, the rate of knee and hip replacement surgeries in Australia is predicted to increase by 276% and 208% respectively [1]. While arthroplasty is generally successful, prosthetic joint infection (PJI) is a catastrophic complication. As per the latest Australian Orthopaedic Association National Joint Replacement Registry (AOANJRR) report, infection is the leading cause of revision surgery in Australia, with 51% of hip revisions and 24% of knee revisions occurring due to infection within three months of the primary surgery [2]. PJI patients have a substantial risk of early death. In Australia, the five-year survival of these patients is just 79%, which is worse than that of many primary cancers, including thyroid, prostate, breast, melanoma, and uterine cancers [3], while the 10-year survivorship is 60% [4]. In a US study, revision arthroplasty for PJI was associated with a fivefold increase in mortality compared with revision arthroplasty for aseptic failures [5]. The quality of life in PJI patients is reported to be worse than in patients with debilitating strokes [6].

Surgery is the most effective option to treat PJI. The Prosthetic Joint Infection in Australia and New Zealand Observational (PIANO) study, which is the largest, multicentre study involving 27 Centres across Australia and New Zealand (including our hospital), reported a 46% failure rate to cure PJI within 24 months using the current standard of care [7]. The surgeries are high-risk, resource-intensive and often require repeated major surgeries. With every admission, the outcomes are increasingly poor, with a higher rate of in-hospital mortality accompanied by inordinate costs that threaten healthcare systems [8–11]. Infection from revision hip replacement has more significant mortality than hazardous procedures such as coronary interventions, carotid surgery, kidney transplants and aseptic arthroplasty revision [12]. In a recent analysis of Australian patients undergoing two-staged revision for PJI cost of treatment was found to be $113,226 at a two-year follow-up [13]. Despite implementing all known patient optimisation and presurgical strategies to reduce PJI, particularly *Staphylococcus aureus* at the surgical site, PJI still occurs [14–17]. Hence, there is an urgent clinical requirement to investigate new preventive strategies to reduce the chances of PJI.

Emerging evidence suggests that the gut microbiome - a range of microorganisms that inhabit the gastrointestinal tract, including bacteria, fungi, viruses, and their genetic components, may play a role in the pathogenesis of musculoskeletal infections [18]. The gut microbiome maintains a homeostatic equilibrium in healthy individuals and resists perturbations. Several factors such as diet, antibiotics, lifestyle, age, gender, compromised immune system, and host genetics can affect the homeostatic configuration of gut microbiota, resulting in a state referred to as dysbiosis [19] or leaky gut, which has been linked to a variety of health disorders, including PJI [18]. Gut dysbiosis can result from either the absence or reduced abundance of beneficial microorganisms, increased abundance of pathogens, altered metabolic functions, or reduced diversity [19]. Preclinical evidence generated using a mouse model representative of clinical PJI [20] showed that susceptibility to PJI was increased by almost 50% in mice with a disrupted gut microbiome before surgery [18]. Furthermore, those mice with a disrupted gut microbial community that went on to develop PJI showed a reduced systemic immune response to infection measured by serum markers and immune cell populations in the spleen [18]. Hence, in the second International Consensus Meeting on Musculoskeletal Infection (MSIS), the need to focus on the gut microbiome as a modifiable factor to treat or reduce the incidence of PJI has been highlighted [21].

Gut dysbiosis is a modifiable condition that can be corrected with appropriate dietary interventions. Profound changes in the gut microbiome can be rapidly achieved by macronutrient changes such as a high-fibre diet or by adding prebiotics or probiotics. A previously published study has demonstrated that a high-fibre diet can alter the gut microbiome favourably in just 24 hours [22]. Probiotics are live microorganisms that confer health benefits when administered in adequate amounts. In contrast, prebiotics are non-digestible fibres that pass through the gastrointestinal tract undigested and are fermented in the colon to produce short-chain fatty acids (SCFAs), such as acetate, propionate and butyrate. These SCFAs, in turn, stimulate the growth and activity of ‘beneficial’ bacteria in the large intestine and have independent health-conferring properties [23, 24].

Resistant Starch (RS) is a type of prebiotic fibre that is found in some legumes and grains (RS 1,2) or produced during the cooking process (RS3) or can be created commercially through the process of chemical cross-linking such as high amylose corn starch (RS 4). Numerous high-amylose corn starches (RS2) are commercially available and can be incorporated easily into the diet to improve gut health. Clinical studies have shown that feeding RS can alter the gut microbiota favourably and reduce the incidence of several diseases [25–29]. Philips et al., in 1995 [30] demonstrated that intake of 39 g resistant starch for three weeks significantly improved the gut microflora and short-chain fatty acid production. Probiotics or prebiotics alone or in combination (synbiotics) have been shown to significantly improve surgical outcomes in liver transplant patients who are at a very high risk of infection, organ rejection and death and in patients undergoing major abdominal surgery [31]. Supplementation was associated with a significantly reduced infection rate, fewer antibiotics prescribed, shorter hospital stays and lower incidence of other complications [31, 32]. These data suggest that adding a prebiotic or probiotics as an adjuvant therapy to the antibiotic regimen may help treat PJI patients more effectively. None of the clinical studies have investigated whether dietary interventions can alter the gut microbiome to improve surgical outcomes in PJI patients. Our study will be the first proof-of-concept study with an overarching objective of identifying a new treatment paradigm for PJI patients. The preliminary evidence linking gut dysbiosis to the incidence of PJI suggests that the outcomes of this study may provide a novel treatment method for this medical condition.

## Study aim

The primary aim of this study is to investigate the effect of a commercially available prebiotic fibre formulation on the gut microbiome in PJI patients planned for a two-stage revision surgery. The secondary aims include the impact of supplementation on blood, tissue and stool biomarkers after 8 weeks of supplementation and treatment outcomes following second-stage revision surgery based on the Delphi criterion.

## Hypothesis

We hypothesise that resistant starch supplementation will improve gut health and treatment outcomes in PJI patients.

## Methods

### Participants

Patients scheduled to undergo two-stage revision for the treatment of PJI at the Royal Adelaide Hospital between January 2024- December 2025 will be recruited for this study. The study has been approved by the Central Adelaide Local health Network Human Research Ethics Committee (CALHN HREC) and all participants will provide written informed consent. The trial has been registered with the Australian and New Zealand Clinical Trials Registry (ACTRN12623001273673).

### Inclusion criteria

Patients will be included if they meet all of the following criteria:

Adult patients with a first-time diagnosis of PJI as per the MSIS criteria and scheduled to undergo two-stage revision at the Royal Adelaide Hospital;Willingness to participate in the study;Sufficiently healthy to undergo two-stage revision surgery.

### Exclusion criteria

Patients will be excluded if they meet any of the following exclusion criteria:

Patients with chronic PJI;Patients who do not consent to the study;Pregnant and breast-feeding women;Patients who cannot tolerate prebiotic fibre;Patients who are immunosuppressed and on dietary restrictions.

#### Study Design and products

In this 8-week, single-centre, double-blind, randomised controlled trial, 80 patients scheduled to undergo two-stage revision surgery for the treatment of PJI will be randomised to receive resistant starch or a placebo containing corn starch. The test product is a commercially available ready-to-mix beverage powder rich in resistant starch (34 g high amylose corn starch, RS2, per serve) available in the Australian market. Patients in the intervention group will receive one sachet of the test product, and those in the placebo group will receive an equivalent amount of ready-to-mix corn-based custard powder for eight weeks. The test and the placebo products will be procured from the market and re-packed in unlabelled plain sachets in a Food Standards Australia New Zealand (FSANZ) approved facility. The treating surgeons will recruit the participants when they present to the Department of Orthopaedics and Trauma for PJI treatment. All patients will be followed up at 2, 4 and 8 weeks after first stage revision and one and two years after the second-stage revision. The study flowchart is shown in Fig. 1.

**Fig. 1 Fig1:**
[figure not shown]
PENGUIN Study flowchart

### Treatment allocation, randomisation and blinding

Patients who consent to participate will be enrolled in the study and assigned a code. Once enrolled, all patients will undergo standard-of-care treatment for their PJI, including optimisation by a multidisciplinary team comprising an anaesthetist, infectious diseases consultant, orthopaedic doctors, joint replacement nurses, dietitian, and post-surgical antibiotic therapy. Using a computer-generated block randomisation plan, one study investigator will randomly assign the patients to the placebo or intervention group. The treating surgeon and the patient will be blinded to the treatment allocation. Supplementation will start soon after the first-stage revision surgery when the patient is well enough to take oral foods. Based on the randomisation plan, the recruited patients will receive one sachet of test or control product mixed with milk, juice or food of their choice once a day for eight weeks. All in-patients will get the product with breakfast, supervised by the study dietitian. On discharge, patients will be given the clinical supplies to complete the supplementation daily for eight weeks. One of the investigators will ensure compliance through regular phone calls.

### Outcomes measures

Primary outcome: The primary outcome is the change in gut microflora between the placebo and the test group after 8 weeks of supplementation.

Secondary outcomes: The study has several secondary outcomes, which are listed below:

Change in faecal calprotectin and short-chain fatty acids within and between cohorts at the end of 8-week supplementation.Change in Interleukin levels (IL-1, IL-6 and IL-10) within and between cohorts at the end of 8-week supplementation.Changes in C-reactive protein, CD4 and zonulin levels within and between the placebo and the test group at the end of 8-week supplementation.Tissue microbiology results will be compared between cohorts during first and second-stage surgery.Treatment outcomes using the Delphi criterion [33] (supplementary file 1) will be reported for the two cohorts at one and two years after second-stage surgery.

### Data collection

The timeline of the follow-up visits and data collection is presented in Fig. 2, and the timeline for measurements is given using The Standard Protocol Items: Recommendation for Interventional Trials (SPIRIT) diagram in Table 1. If any participant fails to continue the study protocol or has less than 80% compliance, the data will be recorded but not included in the final analyses. The results will be presented per protocol as recommended for nutrition studies [34].

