### Adverse outcomes

Patients will be instructed to inform the researchers about any changes or discomfort experienced with the products. However, they will be counselled to help understand normal expectations when starting a prebiotic, e.g., flatulence for a few days. Furthermore, during follow-up visits, the researchers will ask about adverse events which may be related to the intervention. Adverse events, if any, will be recorded and reported in publication. The likelihood of adverse events after administering the test or placebo products is negligible, as both are well-established in-market products.

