### Statistical analysis

There are no studies investigating the improvement in gut microflora in patients with joint infections. Hence, we have based our sample size calculation on the superiority test. We assume a 10% difference in beta diversity between the groups will be a clinically meaningful change. Hence, for a mean difference of 0.1 with an assumed standard deviation of 0.075 at a 5% significance level and accounting for a 10% dropout rate, 80 patients will be required to demonstrate significant changes between the groups at 8 weeks. Normality will be assessed using the Shapiro-Wilk test. Mean and standard deviation or median and interquartile range will be reported. Paired t-test or Wilcoxon test will assess within-group differences, and an Independent t-test, or Mann-Whitney will assess the between-group differences. The secondary outcome measures investigating the outcomes from stool, blood and tissue specimens will be compared between the placebo and test cohorts using a paired t-test or Wilcoxon test for within-group differences and an Independent t-test or Mann-Whitney to investigate between-group differences. Results will be analysed on IBM SPSS 27.

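### The only planned analysis is per protocol: patients who stop or fall below 80% compliance leave every final analysis, and no all-randomised comparison is planned

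*Protocol article*

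**What the plan says.** The rule is in the protocol article under Data collection. It has two triggers, stopping and low compliance: if a participant does not continue the protocol or "has less than 80% compliance, the data will be recorded but not included in the final analyses". The next sentence fixes the presentation: "The results will be presented per protocol as recommended for nutrition studies". A cited recommendation is the only reason given.

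The rule is not limited to the primary outcome. As worded, it also covers the stool and blood biomarkers and the Delphi treatment outcomes at one and two years (Outcomes measures). No section names an all-randomised or sensitivity analysis.

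Under Statistical analysis the framework is superiority ("Hence, we have based our sample size calculation on the superiority test"). Between-group comparisons are an independent t-test or Mann-Whitney test, without covariate adjustment. The sample size allows for loss by "accounting for a 10% dropout rate".

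**The concern.** Randomisation makes the arms comparable at the point of allocation. Whether a patient later stops, or takes less than 80% of the product, is settled afterwards. Removing patients on that basis leaves two groups that chance no longer formed. The article itself gives reasons why removal could be related both to arm and to outcome:

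- **Arm.** Under Adverse outcomes, patients are told what to expect of a prebiotic: "they will be counselled to help understand normal expectations when starting a prebiotic, e.g., flatulence for a few days". If such symptoms are commoner on resistant starch than on custard powder, low compliance may be too.
- **Prognosis.** The Discussion expects many patients to miss longer-term follow-up because they die, their infection does not resolve, or comorbidity rules out the second stage. The Delphi criterion counts infection eradication, freedom from further surgery and absence of PJI-related death. The article does not define failing to continue the protocol. If it covers these patients, the rule removes likely treatment failures from the outcome that is meant to count them.

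The planned two-group tests cannot correct this selection. At stake is whether an observed difference, or its absence, can be attributed to the product.

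**Working it through.** **Inputs from the article.** 80 patients in two arms (1:1 assumed, as the ratio is not stated); difference 0.1, SD 0.075, 5% significance, 10% dropout (Statistical analysis); 46% failure to cure within 24 months (introduction, from a large observational PJI study).

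**Inputs assumed.** Exclusion rates by arm, and outcomes among the excluded. The article gives neither.

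**1. The plan's own figure.** At 80% power, two-sided, n per arm = 2 × (1.96 + 0.842)² × (0.075/0.1)² = 8.8, so 9 per arm, 18 in total, and 18/0.9 = 20 with dropout. The stated 80 is not reproduced. That is a separate matter. What counts here is that with 36 per arm the printed inputs give 99.99% power (normal approximation, two-sided 5%).

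**2. Delphi failure with no true effect.** If overall failure is 46% in both arms, a share r of an arm is excluded and a share f of those excluded fail, then failure among those retained is (0.46 − r·f)/(1 − r).

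| Excluded, arm A v arm B | f | Retained failure, A v B | Shift in favour of A |
|---|---|---|---|
| 20% v 5% | 80% | 37.5% v 44.2% | 6.7 points |
| 5% v 20% | 80% | 44.2% v 37.5% | −6.7 points |
| 10% v 10% | 80% in both | 42.2% v 42.2% | 0 |
| 10% v 5% | 60% | 44.4% v 45.3% | 0.8 points |
| 15% v 5% | 70% | 41.8% v 44.7% | 3.0 points |
| 25% v 5% | 80% | 34.7% v 44.2% | 9.5 points |

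First row: (0.46 − 0.16)/0.80 = 0.375 and (0.46 − 0.04)/0.95 = 0.442. Equal rates protect only if the excluded patients are alike in both arms. With 10% excluded from each but f = 80% in A and 46% in B, the result is 0.38/0.90 = 42.2% v 0.414/0.90 = 46.0%, a 3.8-point shift.

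**3. The same mechanism on the primary scale, no true effect.** If excluded patients are D standard deviations worse than retained ones, the bias is D × SD × (e₁ − e₂), where e₁ and e₂ are the two exclusion rates. For 30% v 10% and D = 1, the bias is 0.075 × 0.20 = 0.015. With 28 and 36 patients retained, SE = 0.075 × √(1/28 + 1/36) = 0.0189, and the two-sided type I error is about 12.5% rather than 5%. For 20% v 10% and D = 1 it is 7.0%. For equal exclusion and equal D it stays at 5%.

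**4. Power of an all-randomised analysis on the printed inputs.** Assume that non-adherent patients gain nothing, so the effect becomes 0.1 × (1 − non-adherent share), with SD unchanged.

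| Non-adherent | Effect | Power, 40 per arm | Power, 36 per arm (10% missing) |
|---|---|---|---|
| 20% | 0.08 | 99.8% | 99.5% |
| 30% | 0.07 | 98.7% | 97.7% |
| 40% | 0.06 | 94.7% | 92.4% |
| 50% | 0.05 | 84.6% | 80.7% |

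**The case against.** The strongest defence is that this is a proof-of-concept study with a mechanistic primary outcome, for which the effect in people who take the product is a fair question. The article also limits differential loss: it excludes patients who cannot tolerate prebiotic fibre, supervises in-patient intake, phones patients after discharge, collects empty packages and blinds patient and surgeon. It describes the expected flatulence as short-lived and adverse events with either product as very unlikely. Differential exclusion is therefore a risk and not something the article shows, and every bias figure above rests on assumed inputs. The 46% also describes PJI under standard care, not two-stage revision specifically. All of this stands, and it is why the illustration runs in both directions and includes zero. It supports keeping a per-protocol analysis. It does not support having no randomised comparison beside it.

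Two stronger readings are tempting, and the article supports neither:

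- **That tolerability harms vanish from the report.** A reader might infer this from exclusion from the final analyses. But Adverse outcomes says that adverse events will be recorded and published and that researchers will ask about them at follow-up visits. Only the scope of the exclusion needs clarifying.
- **That excluding non-compliers leaves the trial underpowered because only 10% loss is allowed for.** The stated inputs are "for a mean difference of 0.1 with an assumed standard deviation of 0.075 at a 5% significance level". On these, power is still above 99% with 28 per arm. A material loss appears only with a larger SD or a smaller difference than those printed.

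An SAP that is not shown does not settle the matter. The article itself fixes the exclusion, so an SAP that follows it carries the same rule and one that departs from it contradicts the published plan.

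**Conclusion.** The point holds. In a superiority trial with unadjusted two-group tests, the stated rule replaces the randomised comparison with one between groups selected on events after randomisation, for the primary outcome, the biomarkers and the Delphi outcomes alike. Neither the direction nor the size of any bias can be derived from the document. Under the assumptions shown, a null product could appear better or worse by 6.7 percentage points on Delphi failure (20% v 5% excluded, 80% failure among those excluded), and the shift is zero if exclusion and failure among the excluded are equal in both arms. The issue is worth correcting before analysis because it governs the main result and the remedy is cheap.

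**What to change.** Change Data collection and Statistical analysis so that:

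- the primary analysis includes all randomised patients in their allocated arm, using every available week-8 sample and Delphi outcome whatever the compliance;
- week-8 samples are sought from patients who stop the product;
- the 80%-compliance per-protocol set is kept as a labelled supportive analysis, with exclusions listed by arm and reason;
- failing to continue the protocol is defined, and the exclusion is stated not to apply to adverse-event reporting.

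**Cost.** The wording is short and the excluded patients' data are already to be recorded. The article does not say that week-8 stool is collected after a patient stops, so continued sampling is a small operational addition. The effect will be diluted to some extent by non-adherence. On the printed 0.1 and 0.075, power remains about 98% with 30% non-adherent and above 80% with 50%. This reassurance depends on those printed values. If the figure of 80 came from other planning values, dilution would cost more and the sample size should be reviewed with them.
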